## Methods

### Setting

This study will be conducted among health centers that are members of OCHIN, Inc., a multi-state network of community health organizations that serve more than 6 million people in rural and medically underserved communities nationwide. OCHIN is a national nonprofit health IT consultancy that provides a fully hosted and shared EHR platform with tailored tools and expertise, including practice management tools, to > 1,000 care delivery sites across 30 states. While all OCHIN members share a single instance of the Epic EHR, each is an independent organization with its own governing board. Conducting this study in a diverse group of health centers improves the likelihood that its results will be generalizable to other primary care settings, an important feature of pragmatic trials.

OCHIN Epic includes a robust suite of tools designed to support collecting and acting on social risk data, many developed through NIH-funded studies.(28, 49–54) One such tool, CR, was made available to OCHIN members in 2022. CR is an integrated EHR tool that supports comprehensive care coordination for high-touch care management, including assessing patients’ social needs, making referrals to community organizations, and tracking referral outcomes to ascertain receipt of community services. Yet at present, an estimated < 10% of health centers use these functionalities to make referrals and track referral outcomes.

All OCHIN health centers that have activated the CR tools in their EHR and participate in one or more CM, population health, or value-based payment model programs that require care coordination of social needs for patients will be eligible for the trial. Such programs include CMS’s care management programs, CalAIM, and patient-centered medical home (PCMH) programs. At least 42 OCHIN member health centers met these criteria at study start-up (November 2023) and another six had adopted CR tools by March 2024. We anticipate that even more health centers do so and thus be eligible for recruitment in early 2025.

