### Main Trial Study Design

Following the formative intervention development described above, a stepped-wedge cluster randomized trial (SW-CRT) will be conducted across 20 OCHIN member health centers, with health centers serving as the clusters. A CONSORT flow diagram outlining the randomization and intervention allocation is provided in Fig. 2.(65) In this trial, the CM teams within each health center will undergo a 12-week implementation support intervention. The stepped-wedge design enables the phased delivery of the intervention to small groups of health centers (four per wedge; five wedges). This approach optimizes study resources while maintaining methodological rigor, leveraging the higher statistical power in this design compared to other CRT designs.(50, 66–68) It also ensures that all participating health centers eventually receive the intervention, potentially enhancing study recruitment.

The 20 recruited health centers will be randomly assigned to one of five wedges using a random number generator independently by the study’s statistician with SAS software for staggered receipt of the intervention. The statistician will have no direct interaction with the health centers and will not be involved in the recruitment of these health centers into the study. Recruitment efforts will be led by the study’s Project Manager and Project Director. These health centers will initially start in the control condition, with each wedge sequentially transitioning (per randomization) to the intervention condition every three months. This process continues until all health centers receive the full 12-week intervention (Table 3). Before receiving the intervention, all study health centers will contribute at least six months of baseline data. After receiving the intervention, all study health centers will continue to be followed until the end of the main trial period, which will span from approximately January 2025 (start of baseline data collection) to June 2027 (end of follow-up for all wedges). The intervention will be delivered to health centers from July 2025 to September 2026. The final wedge to receive the implementation support will be followed for six months in the intervention condition. Participating health centers will receive an impact payment for their involvement.

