### Analyses

Primary outcomes will be measured at six time points for each health center: at baseline and at the end of each of the five wedge’s receipt of the intervention during the CRT. At each time point, all active CM patients receiving care management in a CR program that incorporates social risk activities (e.g. CalAIM, CCM) will be included. The analyses use an open cohort design, as some patients will be measured across multiple time points and others only once. We will identify whether each eligible patient has been screened. We will also identify if patients who screened positive for a social need were referred to a community organization; to the extent possible we will also identify which patients with social needs declined offered referrals. Currently, there is large variability in whether health centers collect data on patients who decline referrals. We will guide on collecting this information as part of implementation support, and we will investigate if we can assess declined referrals as part of our analyses. As the main outcomes are binary and patients are nested in health centers, we will use generalized linear mixed models with a binomial distribution and a logit link and include a random effect for the health center. Patient-level covariates will include age, race/ethnicity, gender, federal poverty level, insurance type, care management program (e.g. CCM; CalAIM), and a health center-level indicator of treatment arm (intervention or control) for each time point.

The analysis for closed-loop referral (secondary outcome) will be limited to patients enrolled in CM that received a referral to a community organization for a social need. Clinical outcomes of hypertension and diabetes control will be limited to enrolled patients with hypertension and/or diabetes, respectively, and a medical visit during the measurement period.

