### Sample Size Calculation

We assessed power (66, 74–76) to detect differences in the percentage of patients with social needs who are referred to community organizations, which is a primary outcome of this study. We used a two-sided significance test with *α* = 0.05. The study’s pre-specified total sample size is 20 health centers with a stepped-wedge open cohort design(77) with five wedges each of four health centers (clusters). Based on preliminary data of high-acuity patients (defined as three or more chronic diseases on the Multimorbidity Weighted index(78–80)) and a completed social risk screen, the expected number of eligible patients is 163 per health center. This number represents the denominator for the primary outcome and the number of patients in each cluster. The proportion of patients with social needs who are referred to services (i.e., the numerator) varies widely, ranging from 10%(81) to 86% in the literature.(24) Therefore, we assume a baseline referral rate of 48%, which is the midpoint between the ranges. We also assume that the intervention would improve clinical-community linkages to between 63.3%(82) and 72%(23) based on other studies. To determine the power of this trial, we examined the absolute differences in screening rates for a range of intraclass correlations, which quantifies the degree of similarity in outcomes within each cluster (health center). We conservatively assumed a cluster autocorrelation and the individual autocorrelation of 0, as there are no sufficient data-driven estimates of these measures,(83) and a block exchangeable decay structure. The cluster autocorrelation refers to the correlation between the population means from the same group at two different periods, while the individual autocorrelation is the correlation between the outcome variable for the same individual at two different periods.(84) If the intervention improves screening rates to 63.3%, as observed in Lian et al. then we would have > 80% power to detect this difference with an intraclass correlation as high as 0.15. If the intervention improves screening rates to 72% as observed in Richman et. al, we would have > 80% to detect this difference with an intraclass correlation as high as 0.30. Power was calculated using the Shiny app(85) for the swCRTdesign(86) package in R.

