## Discussion

Although social determinants are an important consideration for high-risk, medically complex care managed populations, evidence suggests that screening for social needs and providing linkages to community organizations to address identified patient unmet social needs can be hampered by barriers to enabling technologies. As health centers serving systematically underserved populations increase their capacity for documenting and addressing patients’ social needs, it is imperative to identify implementation strategies that support the adoption of enabling technologies and workflows to advance effective clinical-community linkages. While little is known about how to support implementation of technologies specifically focused on clinical-community linkages, evidence is available on implementation strategies that are effective in promoting adoption of other EHR-based tools. Refining these implementation strategies with health center input is expected to support improving the intervention’s ability to conduct social risk screening and place needed referrals among high-risk patients. This is time sensitive, as chronic disease guidelines and value-based payor models are increasingly stipulating screening, referring, and supporting receipt of services for patients’ social needs. To our knowledge, this is the first study to test a set of implementation strategies to improve clinical-community linkages among safety-net primary care health centers. Results will be disseminated to guide primary care clinics on using implementation strategies to further adoption of enabling technologies targeting social risk-targeted care via clinical-community linkages.

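### The primary stepped-wedge model, as written, states no calendar-time effect, so about 60% of a linear background trend would be counted as intervention effect

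*Protocol article*

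**What the plan says.** The Analyses section gives the primary model for both primary outcomes: a binomial mixed model with a logit link and a random effect for health center. Its fixed terms are then named. "Patient-level covariates will include age, race/ethnicity, gender, federal poverty level, insurance type, care management program" is the patient part, and the list ends "and a health center-level indicator of treatment arm (intervention or control) for each time point". Neither this section nor any other part of the article mentions a period, calendar-time or trend term.

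On timing, the same section says: "Primary outcomes will be measured at six time points for each health center", namely baseline and the end of each wedge's receipt of the intervention. Main Trial Study Design has all centers start in control, "with each wedge sequentially transitioning (per randomization) to the intervention condition every three months". The Sample Size Calculation describes "five wedges each of four health centers (clusters") and a test stated as: "We used a two-sided significance test with *α* = 0.05".

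The Discussion says that "value-based payor models are increasingly stipulating screening, referring, and supporting receipt of services" for patients' social needs.

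**The concern.** In a stepped wedge, treatment and calendar time rise together by construction. Here 0, 20, 40, 60, 80 and 100% of centers are in the intervention condition at the six time points. The design is protected by comparing, at the same calendar time, centers that have crossed over with centers that have not. A model uses that comparison only if it contains a time effect. With a center random effect alone, the treatment coefficient is in essence a before-after contrast within centers, and most of the benefit of randomizing the crossover time is lost.

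The words about each time point in the treatment term say that a center's treatment status changes over time. They do not add a time effect.

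At stake is whether a positive result on either primary outcome could be attributed to the implementation support rather than to outside pressure to screen and refer, which the article itself describes as growing.

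**Working it through.** **Inputs from the article.** 20 centers, five wedges of four, six time points (0 to 5), two-sided alpha 0.05. Control referral rate 48%, with targets of 63.3% and 72%. ICC up to 0.15 and 0.30 respectively, cluster and individual autocorrelation 0. There are 163 patients per health center. The article does not say whether 163 is per time point or in total, so I use m = 163 and m = 163/6 = 27.2 per time point.

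**Step 1: the stated power.** With both autocorrelations at 0, the 120 center-by-time means are independent, each with variance s²·[ICC + (1 − ICC)/m], where s² = p̄(1 − p̄) and p̄ is the average of the two rates. The variance of the treatment effect is this quantity divided by S.

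- With period effects, S sums 20·q(1 − q) over time points, q being the share treated: 0 + 3.2 + 4.8 + 4.8 + 3.2 + 0 = 16.
- Without period effects, S = 120 × 0.5 × 0.5 = 30.

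For 63.3%, ICC 0.15, m = 163: s² = 0.5565 × 0.4435 = 0.2468 and the bracket is 0.15 + 0.85/163 = 0.1552. With period effects SE = √(0.2468 × 0.1552/16) = 0.0489, and power = Φ(0.153/0.0489 − 1.96) = 87.8%. The other cases follow in the same way:

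| Scenario | m | With period effects | Without |
|---|---|---|---|
| 63.3%, ICC 0.15 | 163 | 87.8% | 99.0% |
| 63.3%, ICC 0.15 | 27.2 | 82.5% | 97.7% |
| 72%, ICC 0.30 | 163 | 94.4% | 99.8% |
| 72%, ICC 0.30 | 27.2 | 93.0% | 99.7% |

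The stated power above 80% is therefore reproduced with period effects. On a grid of 0.005, the largest ICC that keeps 80% power for 63.3% is 0.16 (m = 27.2) to 0.185 (m = 163) with period effects, and 0.335 to 0.355 without. The stated limit of 0.15 fits the former.

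**Step 2: bias of the model as written.** Take a linear background trend and no intervention effect. For a wedge first treated at time k (k = 1 to 5), mean treated time is (k + 5)/2 and mean control time is (k − 1)/2. The difference is 3 intervals for every wedge. A total rise D over five intervals is D/5 per interval, so the within-center contrast is 3 × D/5 = 0.6·D. The full generalized least squares solution, with ICC 0.15, gives nearly the same (0.0297 to 0.0300 for D = 0.05).

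**Step 3: false-positive rate with no true effect.** Here the center effect is constant over time, as the analysis model assumes. The within-center sum of squares of the treatment indicator, over wedges with 5, 4, 3, 2 and 1 treated times of six, is 4 × (5 + 8 + 9 + 8 + 5)/6 = 23.33. Then SE = √[0.48 × 0.52 × 0.85/(m × 23.33)], which is 0.0075 at m = 163 and 0.0183 at m = 27.2. For D = 5 points, z = 0.03/0.0075 = 4.0 or 0.03/0.0183 = 1.64, and rejection is about 98% or 37%. For D = 2 points, z = 1.6 or 0.66, and rejection is about 36% or 10%.

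A simulation of the logistic model (500 trials per setting, latent-scale ICC 0.15, fixed center intercepts standing in for the random effect) gives:

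| Assumed rise over six time points | Spurious effect | Rejection, m = 27 | Rejection, m = 163 | Mean OR, no period terms |
|---|---|---|---|---|
| 0 | 0 | 4% | 6% | 1.00 |
| 2 points | 1.2 points | 10% | 33% | 1.05-1.06 |
| 5 points | 3.0 points | 32% | 96% | 1.14 |
| 10 points | 6.0 points | 89% | 100% | 1.31 |

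With period terms added, rejection stays between 4% and 7% and the mean OR at about 1.00 in every setting.

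**The case against.** This is a condensed article. It says that covariates will include certain terms, which need not be a closed list, and an unseen analysis plan could add time. No sentence says that time will be left unadjusted. The power figures also look as if period effects were assumed, which points to an omission in drafting. A reader might infer that the team chose to ignore time; the document does not support that. The ICC evidence is itself indirect. Power at ICC 0.15 exceeds 80% without period effects too, and the stated limit of 0.30 for the 72% scenario lies below the 80% limit of either calculation (0.465 or more), so it does not discriminate.

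What stands is that the article lists the model down to insurance type and leaves out the one adjustment on which the design depends. Someone who fits the listed terms gets a confounded estimate.

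The evidence for a trend is also limited. The Discussion describes outside pressure, not rising rates in enrolled centers. That "another six had adopted CR tools by March 2024" might be read as showing growth, but it counts newly eligible centers before the trial, whereas trial centers must already use the tool. The screening outcome might be read as cumulative, and so bound to rise; the wording does not settle this, and turnover in an open cohort could offset it.

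**Conclusion.** The point holds for the model as stated. About 60% of a linear background trend enters the treatment coefficient: upward for a rise, downward for a fall. It would be too strong to say that the whole of a rise is reported as effect.

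The size in this trial is unknown, because the article gives no trend. Under assumed linear rises of 2, 5 or 10 points over the six time points, the bias is about 1.2, 3 or 6 points, against a planned difference of 63.3 − 48 = 15.3 points. False-positive rates for a 5-point rise are about 32-37% at 27 patients per center and time point, and about 96-98% at 163. For a 2-point rise they are about 10% and 33-36%. A reader might take a near-certain false positive as the expected outcome; that needs both a material trend and 163 patients at every time point, and the article establishes neither. With no trend, both models hold roughly 5%.

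**What to change.** In the Analyses section, add a categorical fixed effect for time point to the mixed model for both primary outcomes, and define the intervention effect as the treatment coefficient conditional on time point. The article names no separate model for the binary secondary outcomes; if the same one is used, add the term there too. If the analysis plan already contains it, the article only needs to say so.

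The cost is one sentence, five more parameters and a wider, correct confidence interval. No change to the sample size follows, since the stated power is met with period effects under the article's own assumptions.

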### Sample Size Calculation

We assessed power (66, 74–76) to detect differences in the percentage of patients with social needs who are referred to community organizations, which is a primary outcome of this study. We used a two-sided significance test with *α* = 0.05. The study’s pre-specified total sample size is 20 health centers with a stepped-wedge open cohort design(77) with five wedges each of four health centers (clusters). Based on preliminary data of high-acuity patients (defined as three or more chronic diseases on the Multimorbidity Weighted index(78–80)) and a completed social risk screen, the expected number of eligible patients is 163 per health center. This number represents the denominator for the primary outcome and the number of patients in each cluster. The proportion of patients with social needs who are referred to services (i.e., the numerator) varies widely, ranging from 10%(81) to 86% in the literature.(24) Therefore, we assume a baseline referral rate of 48%, which is the midpoint between the ranges. We also assume that the intervention would improve clinical-community linkages to between 63.3%(82) and 72%(23) based on other studies. To determine the power of this trial, we examined the absolute differences in screening rates for a range of intraclass correlations, which quantifies the degree of similarity in outcomes within each cluster (health center). We conservatively assumed a cluster autocorrelation and the individual autocorrelation of 0, as there are no sufficient data-driven estimates of these measures,(83) and a block exchangeable decay structure. The cluster autocorrelation refers to the correlation between the population means from the same group at two different periods, while the individual autocorrelation is the correlation between the outcome variable for the same individual at two different periods.(84) If the intervention improves screening rates to 63.3%, as observed in Lian et al. then we would have > 80% power to detect this difference with an intraclass correlation as high as 0.15. If the intervention improves screening rates to 72% as observed in Richman et. al, we would have > 80% to detect this difference with an intraclass correlation as high as 0.30. Power was calculated using the Shiny app(85) for the swCRTdesign(86) package in R.

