### Inclusion criteria

Trial health centers will be recruited from OCHIN members that use CR for at least one care management or population health program that stipulates care coordination to address unmet social needs for a monthly average of ≥ 15 enrolled patients. Trial centers must also have care management staff to support programming and provide primary care.

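### The referral power calculation uses 163 high-acuity screened patients per center, which is not the analysed denominator, and its conclusions are labelled as screening rates

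*Protocol article*

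**What the plan says.** The Sample Size Calculation section of the protocol article says that power was assessed for "differences in the percentage of patients with social needs who are referred to community organizations, which is a primary outcome of this study". The design is 20 health centers in "five wedges each of four health centers (clusters"), tested two-sided at 0.05. The cluster size is introduced with "Based on preliminary data of high-acuity patients", defined by three or more chronic diseases together with a completed social risk screen. This gives 163 per health center, and the section adds: "This number represents the denominator for the primary outcome and the number of patients in each cluster". The assumed baseline referral rate is 48%, rising to 63.3% or 72%. Cluster and individual autocorrelations are set to 0. The section then says "we examined the absolute differences in screening rates for a range of intraclass correlations", and both power conclusions are also worded as improvements in screening rates: above 80% at an intraclass correlation (ICC) up to 0.15 for 63.3%, and up to 0.30 for 72%.

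Elsewhere, Outcomes defines the referral endpoint among patients with unmet social needs. Analyses includes all active care-management patients in a CR program with social risk activities, at six time points, and assesses referral in those who screened positive. Neither Inclusion criteria nor Analyses contains a multimorbidity criterion.

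**The concern.** The number that drives the calculation counts a different group from the one to be analysed, in three respects.

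- **Population.** High-acuity patients are not the same as patients enrolled in a CR program.
- **Condition.** A completed screen is not a positive screen, and only positive screens enter the referral denominator.
- **Unit.** A stepped-wedge calculation needs patients per center per time point. The text gives one number per center without saying which is meant.

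The label adds a second difficulty. Screening is the other primary outcome, so the conclusions as printed name an outcome that was not powered. A denominator made up only of screened patients could not serve for it in any case.

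At stake is whether the power statement, including the largest ICC at which it is said to hold, describes this trial's referral comparison.

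**Working it through.** **Inputs from the protocol article.** 20 centers, 5 wedges of 4, 6 time points (Analyses); two-sided alpha 0.05; cluster autocorrelation (CAC) and individual autocorrelation 0; 48% to 63.3% at ICC 0.15 (scenario 1) and 48% to 72% at ICC 0.30 (scenario 2). The number m of patients per center per time point is 163 for the reproduction and an assumption after that.

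**Model.** Generalised least squares on center-period means with fixed period effects and a Wald test. With CAC 0 the periods are independent within a center, so Var = v/16, where v is the variance of one center-period mean. The 16 is the within-period sum of squares of the treatment indicator: with j of 5 wedges treated, each period gives 4 × j(5−j)/5, and summing over j = 0 to 5 gives 4 × (0+4+6+6+4+0)/5 = 16.

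The text does not say how the ICC is applied to a binary outcome, so two conventions are shown, with σ² = p̄(1−p̄):
- A, total variance split by the ICC: v = σ²[ICC + (1−ICC)/m]
- B, within-center variance equal to σ²: v = σ²[ICC/(1−ICC) + 1/m], which is A divided by (1−ICC)

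Power = Φ(Δ/SE − 1.960).

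**Reproducing the stated figure, m = 163.**
- Scenario 1: p̄ = 0.5565, σ² = 0.24681, Δ = 0.153. A: Var = 0.24681 × (0.15 + 0.85/163)/16 = 0.002394, SE = 0.0489, power 87.8%. B: Var = 0.002394/0.85 = 0.002817, SE = 0.0531, power 82.2%.
- Scenario 2: p̄ = 0.60, σ² = 0.24, Δ = 0.24. A: Var = 0.24 × (0.30 + 0.70/163)/16 = 0.004564, SE = 0.0676, power 94.4%. B: Var = 0.004564/0.70 = 0.006521, SE = 0.0808, power 84.4%.

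Both conventions give the stated result of more than 80%, provided 163 is taken per time point.

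**Scenario 1 (ICC 0.15) at other values of m.**

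| m per center per time point | Reading | A | B |
|---|---|---|---|
| 163 | as stated | 87.8% | 82.2% |
| 82 | 50% of 163 positive (assumed) | 86.8% | 81.0% |
| 49 | 30% of 163 positive (assumed) | 85.3% | 79.3% |
| 27 | 163 as a total over six time points (163/6) | 82.4% | 76.0% |
| 15 | illustrative low value | 77.3% | 70.5% |

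**Smallest m for 80% power.** The required SE is Δ/(1.960 + 0.842).
- Scenario 1: SE = 0.153/2.802 = 0.0546, so 16 × SE²/σ² = 0.1933. A: 0.85/m = 0.1933 − 0.15, m = 20. B: 1/m = 0.1933 − 0.1765, m = 60.
- Scenario 2: SE = 0.24/2.802 = 0.0857, so 16 × SE²/σ² = 0.4892. A: 0.70/m = 0.4892 − 0.30, m = 4. B: 1/m = 0.4892 − 0.4286, m = 17.

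(Values of m are rounded up to whole patients.)

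**The case against.** The best defence is that the calculation is sound and not very sensitive to m. With CAC 0, the ICC and the number of centers dominate, and halving 163 costs about one percentage point. ICC 0.15 is the stated upper limit, not the expected value: at ICC 0.10 and m = 15, scenario 1 has 87% power under A. CAC 0 is the plan's own conservative choice: at CAC 0.8, ICC 0.15 and m = 15, power is 91% (A) or 86% (B). The screening wording is very probably a slip, because the opening sentence and the 48% baseline both concern referral. All of this stands. It limits the consequence but does not make 163 the right count.

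Three stronger readings are tempting and are not supported.

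- **Power fails because a center may qualify "for a monthly average of ≥ 15 enrolled patients".** That is a minimum for entry, not an expected size, and power belongs to the trial as a whole. In scenario 1 under A, take one center per wedge at 4 patients and three at 82. The variances are v(82) = 0.24681 × (0.15 + 0.85/82) = 0.03958 and v(4) = 0.24681 × (0.15 + 0.85/4) = 0.08947. Then Var = 1/[4 × (3/0.03958 + 1/0.08947)] = 0.002874 and power is 81%. (The same mix under B gives 75%, against 81.0% with every center at 82.) A large loss requires many centers near the minimum.
- **The true baseline is near 10%, so power is far lower.** The 10% is one end of a literature range. The remark in Setting on low use of these functions counts health centers, not patients. A figure of 57% from a 10% baseline arises only by holding the odds ratio at 1.87, which shrinks the difference to 7.2 points. With the same 15.3-point difference, power at m = 163 is 98% under A.
- **Screening should have its own power figure here.** The section says that it powers one primary outcome. What a condensed article leaves to the full protocol is not a defect.

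**Conclusion.** The point holds as an input and labelling error. The 163 does not count the patients who will form the referral denominator, its time unit is not stated, and the conclusions name the wrong primary outcome. The arithmetic on the stated inputs is correct.

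In size, the 63.3% scenario at ICC 0.15 keeps 80% power only with about 20 (A) to 60 (B) screen-positive CR enrollees per center per time point. The 72% scenario at ICC 0.30 needs about 4 to 17. These thresholds assume CAC 0, six time points and equal center sizes.

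A reader might infer that the trial is underpowered. The document does not show this, because it does not give the number of screen-positive enrollees. Even the direction of the error is not settled: requiring CR enrollment and a positive screen lowers the count, while dropping the chronic-disease criterion raises it. What can be said is that the stated margin in the 63.3% scenario is unverified, and that it is thin under convention B.

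**What to change.** In Sample Size Calculation, replace 163 with the expected number of CR-enrolled, screen-positive patients per center per measurement time point. Network EHR data are the natural source. The formative data review already covers CR enrollment and CR patients with social risk screens, but it does not list positive screens, so a further query may be needed. If the count cannot be obtained, state a range and show power across it.

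Rerun the same software, state that the count is per time point, and restate either the power or the largest ICC at which 80% holds. Change screening rates to referral rates in all three places.

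This costs one data query, one rerun and a wording correction. No additional centers are needed. The only possible drawback is a less favourable stated power or maximum ICC.

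### Setting both autocorrelations to 0 is not conservative in this stepped wedge, so the stated power above 80% is not a floor

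*Protocol article*

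**What the plan says.** The Sample Size Calculation section of the protocol article powers the trial on referral among patients with social needs: 20 health centers in five wedges of four, two-sided 5% significance, 48% at baseline against 63.3% or 72% under the intervention. On cluster size it says that "the expected number of eligible patients is 163 per health center". Noting that adequate estimates of the autocorrelations are lacking, it continues: "We conservatively assumed a cluster autocorrelation and the individual autocorrelation of 0", together with "a block exchangeable decay structure". For the 63.3% scenario the conclusion is that "we would have > 80% power to detect this difference with an intraclass correlation as high as 0.15". The same is said of the 72% scenario up to an ICC of 0.30. No range of autocorrelations is shown.

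The Analyses section gives the remaining design inputs: "Primary outcomes will be measured at six time points for each health center", and "The analyses use an open cohort design, as some patients will be measured across multiple time points".

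**The concern.** The word *conservatively* tells the reader that the unknown autocorrelations can only raise power above the quoted figures. That would be true if power rose steadily with the CAC. In a stepped wedge it does not. A center's treatment status is positively correlated over time, because once it crosses over it stays crossed over. A weak correlation between a center's periods therefore first costs information on the treatment contrast, and only a stronger correlation gives it back through within-center comparison. The individual autocorrelation (IAC) acts in the same direction when the CAC is 0. In an open cohort with repeat measurement, the IAC is unlikely to be exactly 0.

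At stake is how the two ICC limits are read. They are the only power statement in the article and are presented as safe against parameters that the authors could not estimate. The structure label matters for the same reason. Block exchangeable and decay structures are identical at a CAC of 0 but have different worst cases, and the wording joins the two.

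**Working it through.** **Inputs.** From Sample Size Calculation: 20 centers, five sequences of four, 163 patients, 48% against 63.3% (ICC 0.15) or 72% (ICC 0.30), two-sided 0.05. From Analyses: six time points.

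**Assumptions.** 163 applies to each center-period. Period effects are fixed, the test is a z-test, and the variance uses the mean p of the two rates. In the main reading p(1-p) is the residual variance, so the between-center variance is ICC/(1-ICC) times p(1-p).

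**Step 1: reproduce the stated figures at CAC = IAC = 0.** The periods are then independent. With k of the five sequences treated, a period contributes 20 × (k/5)(1 - k/5). Over k = 0 to 5 this sums to 20 × (0.16 + 0.24 + 0.24 + 0.16) = 16. So Var = V/16, where V is the variance of a center-period mean, V = p(1-p) × [ICC/(1-ICC) + 1/163].

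- 63.3%, ICC 0.15: p = 0.5565 and p(1-p) = 0.2468. V = 0.2468 × (0.1765 + 0.0061) = 0.04507. Var = 0.002817 and SE = 0.0531. 0.153/0.0531 = 2.883; minus 1.960 = 0.923; power 82.2%.
- 72%, ICC 0.30: p = 0.60 and p(1-p) = 0.24. V = 0.24 × (0.4286 + 0.0061) = 0.10433. Var = 0.006521 and SE = 0.0808. 0.24/0.0808 = 2.972; minus 1.960 = 1.012; power 84.4%.

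Both stated claims reproduce.

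**Step 2: let a center's periods correlate (block exchangeable).** Let r be the correlation between two period means of one center. For five steps and six time points, Var = V × f(r)/8, with f(r) = (1-r)(1+5r)/(2+5r).

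- f(0) = 0.500, which gives V/16 as in step 1.
- f peaks at 0.542 near r = 0.13, a variance increase of 8.3%.
- f(0.30) = 0.70 × 2.5/3.5 = 0.500, so the loss is recovered only at r = 0.30.

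This shape comes from the design alone. It does not depend on the ICC, the cluster size or the variance convention. With IAC 0 and ICC 0.15, r = CAC × 0.1765/0.1826 = 0.966 × CAC, so the peak is near CAC 0.13 and the break-even near 0.30/0.966 = 0.31.

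For 63.3% at the peak: Var = 0.04507 × 0.5417/8 = 0.003052 and SE = 0.0552. 0.153/0.0552 = 2.770; minus 1.960 = 0.810; power 79.1%. Scanning the CAC, power is below 80% from about 0.06 to 0.22, then 89.7% at 0.5 and 99.7% at 0.8.

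**Step 3: decay structure (correlation CAC to the power of the lag).** A generalised least squares scan puts the 63.3% minimum near CAC 0.28, where the variance is 15.5% above its CAC-0 value. SE = √(0.002817 × 1.155) = 0.0570; 0.153/0.0570 = 2.683; minus 1.960 = 0.723; power 76.5%. It is below 80% from about 0.07 to 0.46.

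**Step 4: the other variance convention.** If p(1-p) is the total variance, V = 0.2468 × (0.15 + 0.85/163) = 0.03831. At CAC 0, Var = 0.002394 and power is 87.8%.

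| Scenario | p(1-p) taken as | CAC 0 | Minimum, block exchangeable | Minimum, decay |
|---|---|---|---|---|
| 63.3%, ICC 0.15 | residual variance | 82.2% | 79.1% | 76.5% |
| 63.3%, ICC 0.15 | total variance | 87.8% | 85.2% | 82.9% |
| 72%, ICC 0.30 | residual variance | 84.4% | 81.5% | 79.0% |
| 72%, ICC 0.30 | total variance | 94.4% | 92.7% | 91.1% |

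**Step 5: which convention was used.** At CAC 0, power reaches 80% at ICC 0.158 and 0.326 with residual variance, and at 0.188 and 0.486 with total variance. The stated 0.15 and 0.30 fit the first pair better. This is an inference; the article does not say.

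**Step 6: IAC at CAC 0.** Here r = IAC × 0.0061/0.1826 = 0.034 × IAC, so the effect is small. For 63.3%, power is 81.3% at IAC 0.5, 80.8% at 0.9 and about 80.7% near 1. It does not fall below 80%, and it leaves the block-exchangeable minimum at 79.1%.

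**Step 7: if 163 were the total over six periods (27.2 per period).** For 63.3%, the residual-variance reading gives only 76% at CAC 0, which contradicts the stated figure. The total-variance reading gives 82.5%, with a block-exchangeable minimum of 79.4%.

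**The case against.** The strongest reply is that nothing was miscalculated, and that stands: both figures reproduce at the stated settings. The dip below 80% is 0.9 points under block exchangeable. It needs one of two possible variance conventions and a CAC between about 0.06 and 0.22, and nothing in the article places the true CAC there. Above about 0.31, zero is indeed on the safe side, often by a wide margin. The planned model has a single center random effect, which implies a CAC of 1, and against that model a CAC of 0 gives low power. A condensed article may also leave a sensitivity grid to the full protocol.

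These points limit the size of the problem but do not make the label true. Choosing a model with one random effect does not fix the actual correlation between periods. The absence of a grid is not the finding; the finding is that the article claims a property the calculation does not have.

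A reader might infer that power simply falls to 77%, that both ICC limits fail, or that the trial is underpowered. The documents support none of these. The 77% end needs a decay structure. The 72% limit survives under block exchangeable. With p(1-p) as total variance and 163 per center-period, every minimum stays above 80%. A reader might also blame the repeat measurements, but a positive IAC alone does not take power below 80%.

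**Conclusion.** The concern holds as a minor error of labelling. Under every variance convention and structure checked, power first falls as the CAC rises above 0, so CAC = IAC = 0 is not the least favourable case and the figures above 80% are not lower bounds. On the reading that best matches the published limits, the 63.3% scenario at ICC 0.15 has a worst case 3.1 points below its zero-autocorrelation value under block exchangeable (82.2% to 79.1%) and 5.7 points below under decay (82.2% to 76.5%). The 72% scenario at ICC 0.30 falls short only under decay, by 1 point. Crossing 80% depends on the inferred variance convention and on 163 applying to each center-period; the direction of the error depends on neither.

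**What to change.** Delete *conservatively*. Name one correlation structure, block exchangeable or decay. State the variance convention and whether 163 is per measurement period. Report the minimum power over CAC 0 to 1.

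On the main reading, the 63.3% scenario would then be given as about 79% worst-case power at ICC 0.15 under block exchangeable. Alternatively, the ICC limit that keeps 80% throughout could be quoted: about 0.147 under block exchangeable or 0.139 under decay. The 72% limit of 0.30 can stand under block exchangeable, where the corresponding value is about 0.308.

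The cost is a rerun of the same power calculation over a grid, a reworded paragraph and a slightly less favourable stated figure. The 20 centers, the patients and the conduct of the trial are unchanged.
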